
#### Secondary outcomes

##### Infant healthcare utilization

Data are abstracted from the child’s EMR at the end of the 18-month follow-up period, including receipt of on-time immunizations and screenings (i.e., lead, hemoglobin, and developmental assessments); infant hepatitis C screening at 18 months among those with perinatal hepatitis C exposure; the number of acute primary care visits (“sick visits”); emergency department utilization and hospitalizations; subspecialist referrals and visits (e.g., Neurology, Ophthalmology, Developmental Medicine); and early intervention referral and enrollment. The proportion of participants who receive these services within the 18-month study period will be compared between the 2 study arms. The mean number of hospitalizations and sick, emergency, and specialist visits will also be compared between the 2 groups.

##### Infant development

This is self-reported at the 6-, 12-, and 18-month follow-up assessment visit using Ages & Stages Questionnaires, 3rd Edition (ASQ-3), a set of 40-item parent-reported age-specific developmental screening questions assessing communication, gross motor, fine motor, problem-solving, and personal-social skills [24]. Domain-specific scores are calculated. Mean ASQ-3 scores, abnormal ASQ-3 scores, and the number of children with any abnormal ASQ-3 scores will be compared between the 2 study arms.

##### Maternal health behaviors

Participants who enroll into CHAMPS while pregnant self-report: duration of breastfeeding at 1, 6, and 12 months; infant sleep positioning at 1, 6, and 12 months; contraception use at 1, 6, and 12 months; and repeat pregnancy within 12 months of follow-up. The proportion of participants who report these behaviors will be compared between the 2 study arms.

##### Maternal psychosocial

This is self-reported at the 1-, 6-, 12-, and 18-month follow-up assessment visits and includes depression using the Edinburg Postnatal Depression Scale [25]; general stress using the Perceived Stress Scale [26]; parenting stress using the Parenting Stress Index [27]; social support using the Social Provisions Scale [28]; and resilience using the Connor-Davidson Resilience Scale [29]. The total score and the subscale scores at 18 months, and the change in scores overtime will be compared between the 2 study arms.

##### Maternal illicit substance use

This will be defined as any and number of positive urine drug screens for illicit substances at the 6-, 12-, and 18-month follow-up assessment visits. Data will be abstracted from the opioid treatment program records. The proportion of participants with any positive screen and the mean number of positive screens at each time point will be compared between the 2 study arms.

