Group WCC sessions diverge from individual WCC in the following ways:*Setting and duration*: Group WCC sessions occur in a dedicated group room at the SUD treatment program and last 2 h. A room divider with a computer and an examination table offers a private area for pediatricians to examine the infant and review history, current issues, and other maternal concerns. The group space itself entails a circle of chairs or pillows on the floor with mats in the middle for infants. There are shelves with children’s books and toys that participants may use. Healthy snacks are provided during the session for the mothers and their children (when age appropriate).*Provider interaction*: Each group is assigned to one pediatrician who will lead all WCC sessions for that group, with a nurse practitioner from the opioid treatment program serving as co-facilitator. All providers involved in delivering group WCC are trained in group facilitation by Centering Healthcare Institute, which emphasizes skills such as reflective listening and strategic questioning as opposed to didactic education. A pediatric nurse assists with immunizations and other procedures.*Content*: A structured, reproducible modular curriculum guides session content, with flexibility based on group needs. Facilitated group discussions provide opportunity for skills building, knowledge sharing, and normalization of early parenting experiences. In addition to standard topics within the *CenteringParenting *curriculum, emphasis on specific clinical topics is tailored to the patient population. Topics were selected and prioritized based on the team’s collective experience as experts in OUD treatment and pediatric primary care and from results from the team’s formative qualitative research conducted with mothers with OUD and pediatric providers [7]. Aspects of Mindfulness Based Parenting [18, 19]—a relational approach developed from the principles of mindfulness and that calls for the full attention of parents when interacting with their children—is also incorporated into each session.*Scheduling*: Sessions are scheduled in advance to reoccur on consistent days and time in coordination with other scheduled groups at the opioid treatment program. Participants who no-show for group WCC are contacted to schedule a routine office-based individual visit. Participants in group WCC are able to schedule acute visits in the office as needed.

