
### Plans to promote participant retention and complete follow-up {18b}

Multiple strategies are used to retain participants over the duration of the study, including (1) providing reminders (e.g., calls, texts) before study data collection visits; (2) limiting participant burden by scheduling data collection study visits when participants are already attending the SUD treatment center; (3) using limited release of medical information forms for EMR abstraction; (4) providing incentives after completion of data collection visits; (5) paying for car ride services (e.g., Uber) and providing parking vouchers to nearby parking garages so participants can park during study visits; (6) collecting contact information of friends and family members who are likely to know the location of subjects should they be temporarily out of contact; and (7) sharing information about the study with staff and providers across hospital departments (e.g., Neonatology, General Pediatrics, Ob/Gyn). In addition, our approach to analyzing the data will allow us to include subjects in analyses who provide partial data due to premature study dropout. Comparisons between study subjects who are retained and who drop out will be conducted to determine biases and non-random patterns of study attrition.

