## Statistical methods

### Statistical methods for primary and secondary outcomes {20a}

#### Quantitative data

Analyses will follow intent-to-treat principles, with participants analyzed according to randomized treatment assignment of the cluster in which they reside. Most analyses will use the individual participant as the unit of analysis, but because randomization is at the cluster level, model-based approaches that account for the correlation between individual participants within a cluster will be used.

Collected data will be summarized in tabular and graphic forms. Demographics and other study variables will be summarized by treatment groups. Mean (SD) or median (interquartile), as appropriate, will be used to describe numerical data, and frequency and percentage will be used to describe the distribution of categorical variables between treatment groups. Two-sample t-test, Mann–Whitney U test, chi-square test, and Fisher’s exact test will be used to compare the distribution of study variables between two-intervention groups as appropriate. Longitudinally collected data will be summarized by intervention groups and data collection time points.

Analysis of variance (ANOVA) and generalized linear and logistic regression models will be used to analyze outcomes measured at one time point, as appropriate. Trajectories of change for outcomes that are repeatedly measured over time will be examined using generalized linear mixed models (GLMMs) and linear, logistic, and negative binomial/Poisson regression models for continuous, binary, and count outcomes. Total scores and subscales from assessments will be used when applicable. The use of GLMM models will allow for an estimation of between-group differences in outcomes at each time point of measurement and will allow for an estimation of changes over time and time by group interactions while accounting for within-subject associations arising from the repeated measures. Clustering of participants will be accounted for in the GLMMs models by including cluster as a random or fixed effect and in the generalized models by using robust variance estimates. Potential covariates will be selected based on consideration of study arm balance and potential confounders for an outcome previously reported in the literature.

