### Adverse event reporting and harms {22}

Monitoring and reporting of adverse events will be conducted from the time of consent to trial entry until the end of the trial. Adverse events and harms will be collected non-systematically, i.e., through spontaneous reporting of events. Research personnel will be asked to report unanticipated problems and adverse events, including serious adverse events such as an important medical event, hospitalization, or death of a mother or of a child of an enrolled mother, within 24 h of learning of the event. If known, the reason for the event should also be reported. The principal investigator, who is a pediatrician, will review the event within 24 h. The purpose of the review will be to assess if there is any reason that the event can be considered attributable to the study’s intervention. If the study is considered a causative factor, the report will be forwarded to the other principal investigator. The principal investigators will then determine the appropriate response through consultation with appropriate individuals. Adverse events will be documented in the participant file and reported to the appropriate IRB. It is believed that rarely would the study be considered a possible cause, but the establishment of the review procedure should assure that harm potentially attributable to the study is not missed and that any identified harm is addressed and avoided going forward. The review procedures developed for this study consist of weekly meetings with the opioid treatment program clinical team to review specific issues that were identified in the group visits. Issues such as maternal substance use or relapse, child safety concerns, and indications for child protective service involvement as well as housing, family safety, and other concerns are addressed with the team and clinical therapists, social workers, navigators, or peer support specialists are engaged to address issues.

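### Maternal illicit substance use is compared as any positive and a raw count of positive urine screens, with no denominator of screens done, so unequal testing between arms could look like unequal use

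*Protocol article*

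**What the plan says.** Under Secondary outcomes, Maternal illicit substance use, the protocol article defines the outcome as "any and number of positive urine drug screens for illicit substances" at the 6-, 12- and 18-month assessment visits. The source is clinical: "Data will be abstracted from the opioid treatment program records". The arms are compared on "The proportion of participants with any positive screen and the mean number of positive screens at each time point".

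Under Quantitative data, the repeated-measures analysis lists "negative binomial/Poisson regression models for continuous, binary, and count outcomes", so a count model is available. No offset or exposure term is mentioned. The article states no screening schedule, look-back window or share-positive measure, and no rule for a mother with no screens in a window. Section {18b} says that the approach can "include subjects in analyses who provide partial data due to premature study dropout", and section {20c} says that missing-data patterns will be examined and imputation considered.

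Three other statements bear on contact with the program. Group visits take place on-site there and are scheduled "in coordination with other scheduled groups at the opioid treatment program" (section {11a}). Control visits are at a practice five blocks away (Control description). Section {22} describes "weekly meetings with the opioid treatment program clinical team to review specific issues that were identified in the group visits".

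**The concern.** A count of positive screens reflects both how often a mother uses and how often she is tested. When the study itself fixes the number of tests, the second part is the same for everyone. Here the screens come from routine clinical records, so their number depends on program practice and on how long the mother stays in treatment. A mother who leaves partway through a window has fewer screens, and so a lower expected count, at the same level of use. Any positive has the same weakness in a milder form, because more screens give more chances of at least one positive.

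The arms could plausibly differ in contact with the program: intervention visits are held there, and issues raised in group visits are discussed with its clinical team. If testing or part-window time differed as a result, the planned comparison could report a difference in illicit use, in either direction, where none exists. Without the number of screens done by arm, a reader could not separate the two explanations. For a sensitive outcome in this population, that ambiguity is worth removing.

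**Working it through.** **Plan's own figure.** The protocol gives no power or precision figure for this outcome. Its general figure (0.54 SD, 54 per arm, two-sided 5%) reproduces: power = Φ(0.54·√(54/2) − 1.96) = Φ(0.846) = 0.80. Only the 54 per arm is used below.

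**Step 1: the measures as functions of testing.** Let a mother have *m* screens in a window, each positive with probability *p*.

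- Expected number of positives = *m·p*.
- Probability of any positive = 1 − (1 − *p*)^*m*.
- Expected share positive = *m·p*/*m* = *p*.

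The first two rise with *m* at fixed *p*; the third does not. A mother in the program for a fraction *f* of the window has about *f·m* screens and expects *f·m·p* positives, so part-window time acts in the same way.

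**Step 2: a fixed-*p* illustration.** Assume *p* = 0.20 in both arms, with 6 screens in one and 8 in the other. Mean positives are 6 × 0.20 = 1.2 and 8 × 0.20 = 1.6, a ratio of 1.33. Any positive is 1 − 0.8^6 = 73.8% and 1 − 0.8^8 = 83.2%. The share positive is 20% in both.

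**Step 3: false-positive rate, by simulation.** All inputs except the arm size and number of clusters are assumptions:

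- no true difference in use; 54 mothers per arm in 13 clusters (11 of 4, 2 of 5); ICC 0;
- positivity varies between mothers as Beta(0.4, 1.6), mean 0.20;
- 6 (monthly) or 26 (weekly) routine screens in a 6-month window;
- one arm has on average 10%, 20% or 30% more screens, with the same positivity;
- Poisson log-rate ratio with cluster-robust variance, t with 24 df, nominal two-sided 5%, no Benjamini–Hochberg step; 6000 trials per setting.

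| Extra screens in one arm | Ratio of mean positives | Rejection, 6 screens | Rejection, 26 screens |
|---|---|---|---|
| 10% | 1.10 | 5.6% | 7.6% |
| 20% | 1.20 | 10.0% | 12.1% |
| 30% | 1.30 | 16.1% | 18.8% |

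Repeat runs with separately written code agree within one percentage point. Any positive moves by at most 4 points: with 30% more screens it goes from 49.5% to 53.5% (6 screens) or from 70.2% to 73.0% (26 screens). The shift is smaller than in step 2 because positivity varies between mothers.

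**Step 4: with a denominator.** In the same settings, a count model with log screens as offset rejects in 4.5% to 5.3%. In a separate simulation of 6 screens against 6 to 12, the per-mother share positive rejects in 4.7% to 5.1%. Both are near the nominal 5%.

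**The case against.** **No documented cause of unequal testing.** All mothers in both arms are treated by the same program, with the same wraparound services. Group visits are at most eight over 18 months (ages 1, 2, 4, 6, 9, 12, 15 and 18 months). This stands: the concern is conditional.

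**The weekly review.** A reader might infer that this review would generate extra screens for intervention mothers. The protocol does not say so. The response it describes is that "clinical therapists, social workers, navigators, or peer support specialists are engaged to address issues", and no urine screen is mentioned. Neither its effect on testing nor its size can be derived from the document.

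**Retention.** A reader might also infer that mothers who leave the program are counted as having no positives. No such rule is stated. Section {18b} concerns study dropout, and the mixed models and section {20c} are compatible with treating unobserved windows as missing. Under the same positivity and screening assumptions, windows of mothers who had left treated as missing give a ratio of 1.00 to 1.01 and rejection of 4.7% to 5.4%, at 90% against 80% or 70% retention, when leaving is unrelated to use. So whole-window leaving does not by itself produce the artefact; part-window time still can. The average outpatient stay of 3 to 4 years may keep even that small.

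**One specimen per visit.** The definition places the screens at the assessment visits, which could mean a single specimen. Listing both any and number suggests several screens, but several substances tested on one specimen could also give a count above one. The text does not settle this. On the one-specimen reading the testing-frequency problem disappears.

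**Detail for an analysis plan.** An offset or a look-back window can properly be left to a plan not shown, and silence on an offset is not a decision against one. However, the article does name the two quantities to be compared. Neither has a denominator, and an offset in the count model would not repair the any-positive proportion.

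**Conclusion.** The point holds as a minor one on a single secondary outcome; no primary conclusion depends on it. The compared quantities, as named, depend on the number of screens done whenever a window contains several clinical screens. That follows from the arithmetic and needs no assumed figure. Whether it biases this trial depends on an arm difference in testing or in part-window program time, which the protocol neither shows nor rules out. The direction is unknown.

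The size given (ratio 1.10 to 1.30, nominal rejection roughly 6% to 19%) rests wholly on the assumed 10% to 30% excess, screening frequency and positivity. At a 10% excess the inflation is slight. The Benjamini–Hochberg adjustment in the plan would lower these rates by an amount that depends on the other tests. The documents do not support the stronger conclusion that the planned analysis is biased toward a particular arm.

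**What to change.** Abstract the number of screens done per mother and window along with the positives. In place of the raw mean count, compare positives out of screens done, either as the per-mother share positive or with a binomial model that allows for clustering and repeated windows. Any positive can be kept as a description if shown beside the screens done. Report screens done and mothers still in the program by arm and window. Treat windows with no screens as missing, not as negative. State the look-back window, or say that one specimen per visit is meant.

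The cost is one extra abstraction field from records already being read. The change does not remove all bias. For-cause screens may be more often positive than routine ones, so a difference between arms in for-cause testing would still distort the share. So would leaving that is related to use and differs by arm. Where the records give the reason for a screen, a sensitivity analysis limited to routine screens would address the first of these, at the price of a second field.

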##### Maternal sensitivity/responsiveness

This is self-reported at the 12-month follow-up assessment visit using the Maternal Responsiveness Questionnaire [30], which assesses the extent to which mothers engage with and respond to their infants. The measure yields three scored subscales (responsiveness, non-responsiveness, and delayed responsiveness). At the 18-month follow-up assessment visit, the Coping with Toddlers’ Negative Emotions Scale [31] is completed which measures the degree to which mothers perceive themselves as reactive to their children's negative affect in distressful situations. Six subscales are derived that reflect the specific types of coping response parents tend to use in such situations. Mean subscale scores for each questionnaire will be compared between the 2 study arms.

### Participant timeline {13}

### Sample size {14}

Assuming 150 births in the opioid treatment program over an 18-month recruitment period, > 90% rate of maternal legal guardianship at birth, 80% study participation rate, and equivalent group allocation (50%), we expect to enroll 108 participants (n = 54 per study arm) during the project period. A sample size of 54 per study arm will produce a two-sided 95% CI with a distance from the standardized difference in means between two arms to the limits that are equal to 0.38. Additionally, with a sample size of 54 per study arm, a two-sided test for the time-averaged difference between two means in a repeated measures design with a significance level of 0.05 will have 80% power to detect a standardized difference in means of 0.43 in a design with 4 repeated-measurements taken over the 18-month period and with between level correlations of 0.5. A sample size of 54 per study arm will give us 80% power to detect a standardized difference in means of 0.54 (effect size) between two arms using a two-sided two-sample t-test with a significance level of 0.05. Of note, we were unable to find reported data about the cluster effect of different birth months. However, we expect only a negligible cluster effect for birth-month, and so assumed no to negligible intra-cluster correlation coefficient (ICC; 0 to 0.05) to perform the power calculations, which is almost equivalent to performing simple random sampling. However, we preferred the design of cluster random sampling to simple random sampling to account for the effect of birth-month if there is any.

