**Methods:**

CHAMPS is a single-site 2-arm cluster randomized controlled trial. A total of 108 mother–child dyads will be enrolled into the study. Twenty-six clusters of approximately 4 mother-infant dyads each will be randomized 1:1 to one of two study arms (intervention or control). Clustering will be based on child’s month of birth. In the intervention arm, group well child care will be provided on-site at a maternal substance use disorder treatment program. Mother–child dyads in the control arm will receive individual well child care from one nearby pediatric primary care clinic. Dyads in both study arms will be followed prospectively for 18 months, and data will be compared between the two study arms. Primary outcomes include well child care quality and utilization, child health knowledge, and parenting quality.

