### Trial design {8}

This is a single-site cluster randomized controlled trial. One hundred eight pregnant and parenting women receiving treatment for OUD from one single opioid treatment program will be enrolled into the study. Twenty-six consecutive clusters—based on the one-month birth intervals of participants’ infants—of ~ 4 dyads will be randomized in a 1:1 ratio to one of two study arms. Thirteen clusters will be randomized to individual WCC (control group), and 13 birth clusters will be randomized to group WCC (intervention arm), with concealment of randomization from participants until after they have completed their initial enrollment study visit, or, for those who are pregnant at time of enrollment, immediately following delivery. Randomization by birth month was selected to ensure a close age range among infants receiving group WCC together in the intervention arm. Blocking or stratification was not used in the randomization. Dyads in both study arms will be followed prospectively for 18 months, and data will be compared between the two study arms. Primary outcomes include well child care quality and utilization, child health knowledge, and parenting quality. We hypothesize that at the end of the study period, participants in the intervention arm will have increased WCC engagement, knowledge about parenting, and maternal responsiveness compared to participants in the control arm.

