### Eligibility criteria {3}

Inclusion criteria for screening for and consent into the trial are as follows: (1) 18 years or older, (2) at least 28 weeks pregnant or parenting a child less than 12 months of age, (3) receiving treatment for OUD from the recruitment opioid treatment program, (4) ability to read and speak English, (5) plans to parent infant after delivery (if pregnant), (6) intent to seek pediatric care within the affiliated health system, and (7) intent to remain in the local area for the next 2 years. Exclusion criteria include (1) inability to speak English, (2) plans to move outside of the local area in the next 2 years, (3) plans to not parent infant after delivery, and (4) plans to seek pediatric care outside of the affiliated health system.

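### The enrolment projection does not match the 26 birth-month clusters, and the stated 80% power at a difference of 0.54 holds only at an ICC of 0, not over the stated range of 0 to 0.05

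*Protocol article*

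**What the plan says.** The protocol article's Sample size section builds enrolment from three inputs: "Assuming 150 births in the opioid treatment program over an 18-month recruitment period", a "> 90% rate of maternal legal guardianship at birth" and an "80% study participation rate". It concludes that "we expect to enroll 108 participants (n = 54 per study arm) during the project period". From 54 per arm it gives a confidence-interval half-width of 0.38, a detectable standardized difference of 0.43 for four repeated measurements correlated at 0.5, and one of 0.54 for a two-sample t-test at 80% power. It adds that an ICC of 0 to 0.05 was assumed for these power calculations.

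The cluster structure is given elsewhere. The abstract says "Twenty-six clusters of approximately 4 mother-infant dyads each will be randomized 1:1 to one of two study arms". Trial design calls them "Twenty-six consecutive clusters" defined by one-month birth intervals, and says "Thirteen clusters will be randomized to individual WCC (control group), and 13 birth clusters will be randomized to group WCC". Intervention description expects 3 to 5 dyads per birth-month group. Eligibility criteria admit women who are "at least 28 weeks pregnant or parenting a child less than 12 months of age", and Intervention description explains that infants already born at enrolment are also grouped by birth month.

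**The concern.** Two sets of stated figures do not meet.

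- **Enrolment against clusters.** The projection counts births in an 18-month window only. Spread over those months it gives 6 dyads per birth month, above both the stated cluster size of about 4 and the expected 3 to 5 per group. The 26 consecutive birth months must therefore reach outside the 18-month window, but births outside it do not enter the projection.
- **ICC range against printed power.** The section says that a range of ICC values was assumed but prints a single detectable difference. If that figure applies only at the lower end of the range, the reader is told that 80% power covers assumptions under which it does not hold.

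At stake are a credible expected cluster size, which any ICC above 0 needs, and an honest statement of the effect that the trial can detect. The statistical methods section commits to analyses that account for clustering, so the detectable difference should be stated on that basis.

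**Working it through.** **Inputs.** From Sample size: 150 births, 18 months, guardianship taken as 0.90 (stated as above 90%), participation 0.80, 54 per arm, two-sided 0.05, 80% power, ICC 0 to 0.05. From the abstract and Trial design: 26 one-month clusters. From Eligibility criteria: entry from 28 weeks of pregnancy until the child reaches 12 months.

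**1. Reproduce the plan's figures.**
- Enrolment: 150 × 0.90 × 0.80 = 108. Agrees.
- CI half-width: 1.96 × √(2/54) = 0.377, or 0.382 with the t quantile. Agrees with 0.38.
- t-test: (1.960 + 0.842) × √(2/54) = 0.539, or 0.544 with the noncentral t. Power at 0.54 is 80.1% (normal) or 79.4% (t). Agrees with 0.54.
- Repeated measures: (1.960 + 0.842) × √(2/54 × (1 + 3 × 0.5)/4) = 0.426. Agrees with 0.43.

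All of these use 54 per arm with no design effect, that is, ICC 0.

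**2. Enrolment per birth month.**
- Births per month: 150/18 = 8.33. Dyads per month: 108/18 = 6.0.
- Twenty-six months at that rate: 26 × 6 = 156 dyads.
- Stated structure: 108/26 = 4.15 per cluster, which agrees with about 4 and with 3 to 5 per group.
- Average yield needed: 108/(26 × 8.33) = 50% of births, against 0.90 × 0.80 = 72% in the projection.

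**3. Birth months that can enter.** Infants may be born up to 12 months before recruitment opens. Women may enter at 28 weeks, so with a 40-week term (my assumption) births run to 12 × 7/30.44 = 2.8 months after it closes. The span is 12 + 18 + 2.8, or about 33 birth months, so 26 is feasible. At 8.33 births per month that span holds about 273 births; the projection counts 150.

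**4. Detectable difference over the stated ICC range.** Design effect DE = 1 + (m − 1) × ICC, for mean cluster size m. Standard error of the standardized difference = √(2/54 × DE). Power is from the noncentral t, with either 106 degrees of freedom (individual level) or clusters minus 2 (cluster level; my choice, not stated in the article).

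| Design | ICC | DE | Detectable at 80%, individual df | Detectable at 80%, cluster df | Power at 0.54, individual / cluster df |
|---|---|---|---|---|---|
| 26 × 4.15 | 0 | 1.00 | 0.544 | 0.562 | 79% / 77% |
| 26 × 4.15 | 0.02 | 1.06 | 0.561 | 0.579 | 77% / 74% |
| 26 × 4.15 | 0.05 | 1.16 | 0.585 | 0.605 | 73% / 71% |
| 18 × 6 | 0 | 1.00 | 0.544 | 0.574 | 79% / 75% |
| 18 × 6 | 0.05 | 1.25 | 0.608 | 0.642 | 70% / 65% |

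The 18 × 6 rows show sensitivity to cluster size only. Cluster sizes are taken as equal.

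**The case against.** The strongest reply is that the sample size section projects a total and does not derive clusters. The number of clusters follows from which birth months may enter, and the eligibility window allows about 33. Twenty-six clusters, about 4 per cluster and 3 to 5 per group all agree with one another. A 50% average yield need not contradict 72%, because months at either end of the window are only partly exposed to recruitment, and some mothers of older infants may use paediatric care outside the affiliated system and so be ineligible. This stands, and it rules out three stronger readings that a reader might infer.

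- **That the plan implies 18 clusters of 6.** It does not. That follows only if every enrolled child is born within the 18 months, which the eligibility rule does not require.
- **That the printed power rests on the cluster count.** It does not. The figures of 0.54, 0.43 and 0.38 all come from 54 per arm at ICC 0; replacing 26 by 18 would change none of them.
- **That the 1:1 split of clusters is at material risk,** for instance 7 against 11. This needs enrolment to stop after the first 18 listed clusters, which the article nowhere says. The enrolment stopping rule and the realised split are details that a condensed article may leave out.

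The reply does not reach two things. Opening the window to earlier births makes 26 clusters possible but leaves those births out of the projection. And the mismatch between the stated ICC range and the printed power is there even if 26 clusters is accepted without question.

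It is also fair to say that part of the rise, 0.544 to 0.562 at ICC 0, comes only from using cluster-level degrees of freedom. For that reason both versions are shown.

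**Conclusion.** The point holds in two limited parts.

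First, the enrolment projection and the cluster structure rest on different sets of births. The stated 26 clusters are feasible and no single figure is miscalculated, but the article does not connect 6.0 dyads per birth month with clusters of about 4.

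Second, the power statement is wrong as written. It claims an assumed ICC of 0 to 0.05, but 80% power at 0.54 is reached only at ICC 0 without adjustment for clustering. With the plan's own 26 clusters, the upper end of the range gives a detectable difference of about 0.585 to 0.605 and power at 0.54 of about 73% to 71%, according to the degrees of freedom. If enrolment instead filled 18 clusters of 6, the detectable difference at ICC 0.05 would be about 0.61 to 0.64.

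The size is modest: a loss of 0.04 to 0.06 in standardized units against the stated 0.54 for the planned design. It rests on equal cluster sizes, the usual design effect and 54 analysed per arm. The feasibility of 26 clusters also rests on an assumed 40-week term.

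**What to change.** 1. Base the enrolment projection and the expected number and size of clusters on one set of assumptions. Include infants born before recruitment opens and those born after it closes, say which birth months the 26 clusters cover, and give the expected yield per birth month. Bring the abstract, Trial design, Intervention description and Sample size sections into line with it.
2. Restate the t-test detectable difference over the stated ICC range. For 26 clusters of about 4.15 this is 0.54 at ICC 0 to about 0.585 at ICC 0.05 with individual-level degrees of freedom, or 0.56 to 0.605 with cluster-level ones. Say which degrees of freedom are used.
3. Label the 0.43 and 0.38 figures as ICC 0 values, or recompute them on the same basis.

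The cost is wording and recalculation only. No extra participants or design change are needed; the downside is a slightly less favourable stated detectable difference.
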